Residents who sign the informed consent will participate in the research study starting in January 2011. The research study will consist of 2 phases. In the first phase, half of the study subjects will be randomized to wearing an activity monitor with feedback, and half will be randomized to wearing an activity monitor with no feedback (blinded/control group). This phase will last for 6 weeks. Immediately following the randomized phase, all subjects will be unblinded and wear the activity monitor with feedback. The second phase will be a team competition between the 3 classes of residents (interns, juniors, and seniors). The teams will compete on average number of steps per week for each team. The team competition will last for 6 weeks.

Randomization: Study participants will be randomized in late December to either the intervention arm (activity monitor with feedback) or the control arm (activity monitor with no feedback). The randomization will be stratified by class year (intern, junior, senior).

Parameters to be measured:

The parameters that will be measured for all Be Fit program participants at baseline and at the end of the program are listed in the table below. The survey will collect data on health habits, including smoking, nutrition, physical activity, and sleep.

|  | Baseline  (July-November 2010) | End of program  (May 2011) |
| --- | --- | --- |
| **Physical assessment:** Blood pressure and heart rate, weight, BMI, body fat, waist circumference | X | X |
| **Blood draw:** Fasting lipids | X | X |
| Survey (completed by participant) | X | X |

For those Be Fit participants who enroll in the research study, we will collect data measured by the activity device worn from January through May 2011. The activity device records data on number of steps per day, number of calories burned per day, number of hours slept per night, and number of times awakened per night.

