Team competition phase: Immediately following the randomization phase, all study participants will be unblinded and able to view the Fitbit feedback both on the device and on the website. The control group will be given a password to be able to log on to their personalized Fitbit website. The residents will be divided into 3 teams based on their class: interns, juniors, or seniors. The teams will compete on the average number of steps per week. The team standings will be displayed on the Fitbit website that will be viewed by each study subject. Teams will compete for 6 weeks.

Data to be collected:

Physical assessment*:* All residents who enroll in the Be Fit program will be asked to attend a physical assessment at baseline (between July and November 2010) and at the end (May 2011). All physical assessments will be conducted prior to 10 o’clock in the morning. During these visits, study staff collect weight, height, waist measurements, body fat, blood pressure, and heart rate.

Fasting blood test*:* During each physical assessment, residents enrolled in Be Fit undergo a fasting blood test for lipids. Residents are asked not to have anything to eat or drink after midnight the day before the test.

Survey: All residents enrolled in Be Fit will complete a survey at baseline and at the end of the program. The survey collects information on smoking history, physical activity, and nutritional habits. Age, sex, race/ethnicity, marital status, education level, and care for dependents at home (children, disabled/ill spouse, parent, or child) will be recorded on the survey. The survey also includes a scale that measures psychological stress, called the Schwartz Outcome Scale-10 © (SOS-10 TM). The SOS-10 is a 10 item survey tool to determine a person’s distress level. It is not a diagnostic instrument and cannot be used for making psychiatric diagnoses. The scores range from 0 to 60. Higher scores reflect better psychological health and lower scores indicate emotional distress and lower levels of psychological health. There is a cut off score of 43, and a change of 8 points or greater are a reliable indicator that a person’s psychological status has either improved or deteriorated.

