Data from Fitbit website: Only residents who enroll in the research study will be given a Fitbit activity device. All activity data and sleep data recorded during the study period will be collected. The Fitbit website provides individual data on the number of steps per day, the number of calories burned per day, and the number of hours slept per 24 hour period. This data will be collected from all study subjects during both the randomized phase and the team competition phase of the study.

Study endpoints:

Primary endpoint: The primary endpoint of the study will be average activity level per resident as measured by number of steps per day. In the randomized phase, the average number of steps per day in the intervention group (Fitbit + feedback) will be compared to the average number of steps per day in the control group (Fitbit without feedback). In the second phase, we will compare the change in the average number of steps for each participant compared to their own baseline number of steps from the first phase.

Secondary endpoints: Secondary endpoints will be change in weight during the study period and number of hours of sleep per 24 hour period for each resident. Survey data will be used to examine reported changes in physical activity levels, nutritional habits, and sleep habits. The survey data will also provide data from the SOS-10 scale on change in psychological stress.

Statistical methods:

In the randomized phase, the average number of steps per day in the intervention group (Fitbit + feedback) will be compared to the average number of steps per day in the control group (Fitbit without feedback) using a two-sample t test or a Wilcoxon rank sum test whichever is more appropriate. To determine whether team competition increases activity level, the primary and secondary endpoints from the second phase will be compared to results from the first phase using paired t-tests. The changes in primary and secondary endpoints during study periods will be compared between the two randomization groups using a two-sample t test, and compared among the residency year groups using an analysis of variance approach. To determine if the average hours of sleep per week is associated with changes during study period, Pearson or Spearman correlation coefficients will be used to summarize the correlation between sleep time and change in weight/number of steps.

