Power analysis: For the randomization phase, a sample size of 50 in each group will have 84% power to detect a difference in means of 1200 steps assuming that the common standard deviation is 2000 steps using a two group t-test with a 0.05 two-sided significance level.

For studies involving treatment or diagnosis, provide information about standard of care at Partners (e.g., BWH, MGH) and indicate how the study procedures differ from standard care. Provide information on available alternative treatments, procedures, or methods of diagnosis.

This study does not involve treatment or diagnosis of a medical condition or illness.

Describe how risks to subjects are minimized, for example, by using procedures which are consistent with sound research design and which do not unnecessarily expose subjects to risk or by using procedures already being performed on the subject for diagnostic or treatment purposes.

The risk associated with this research is minimal. The principle investigator oversees all study staff to ensure that procedures are followed which are consistent with sound research design and do not expose subjects to unnecessary risk. The study does not offer a diagnosis or treatment to subjects. The procedures in study were developed using standard nutrition and fitness guidelines and recommendations.

Describe explicitly the methods for ensuring the safety of subjects. Provide objective criteria for removing a subject from the study, for example, objective criteria for worsening disease/lack of improvement and/or unacceptable adverse events. The inclusion of objective drop criteria is especially important in studies designed with placebo control groups.

Subjects will be withdrawn from the study if they leave their employment at MGH or if they request to be removed from the study.

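### Step change is tested by arm and by class year in separate one-factor analyses; a single model with both factors would be more precise, at almost no cost

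*Protocol*

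**What the plan says.** Under Study endpoints, the protocol defines phase 2 step change as each participant's average against that person's own phase 1 average. Statistical methods then gives two comparisons of the changes in one sentence: between the randomized groups by a two-sample t test, and "compared among the residency year groups using an analysis of variance approach".

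The arms differ in what changes. Under Randomized phase, controls see no measurements on the device or website. Under Team competition phase, "all study participants will be unblinded and able to view the Fitbit feedback both on the device and on the website", and the competition between the three classes begins.

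On allocation, the protocol says "half of the study subjects will be randomized to wearing an activity monitor with feedback", with the other half wearing a device without feedback, and "The randomization will be stratified by class year (intern, junior, senior").

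The only power statement concerns the randomized phase: "a sample size of 50 in each group will have 84% power to detect a difference in means of 1200 steps". It takes an SD of 2000 steps in both arms and a two-sided t test at the 0.05 level.

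**The concern.** Each half of the sentence names one factor. A two-sample t test cannot carry class year, and the parallel clause for the analysis of variance names only residency year. Read that way, neither comparison uses both factors that structure the trial.

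For steps this matters because the design builds in a possible arm difference in change. Controls move from no feedback to feedback plus competition; the feedback arm moves from feedback to feedback plus competition. If feedback works, the two arms' mean changes differ within every class, and an analysis on class year alone counts that split as unexplained variation. At stake is the precision of the comparison among classes, which are also the competing teams. By the same logic, any class-year difference in change goes into the error of the two-sample t test between arms. The protocol gives no expected class difference, so that side cannot be sized.

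**Working it through.** **Inputs from the protocol (Power analysis; Randomization).** 50 per arm; planned difference 1200 steps; SD 2000 steps; two-sided 0.05; 1:1 allocation stratified by class year.

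**Assumed, because the protocol does not give them.** The correlation ρ between a participant's phase 1 and phase 2 averages; additive effects of feedback and competition; 33 residents per class (about 100 over three classes); arms balanced within class.

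**1. The protocol's own figure.** Noncentrality = 1200 / (2000 × √(2/50)) = 1200/400 = 3.0. The normal approximation gives 85.1% and the exact noncentral t with 98 df gives 84.4%. The stated 84% reproduces.

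**2. Variance of change within arm and class.** Var = 2000² × 2(1 − ρ), which is 4,000,000, 2,400,000 or 1,600,000 at ρ = 0.5, 0.7 or 0.8 (SD 2000, 1549 or 1265).

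**3. Variance added by omitting arm.** With balanced arms whose mean changes differ by D, the added variance is D²/4. For D = 1200 this is 360,000; for D = 600 it is 90,000.

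**4. Inflation and power.** Inflation = 1 + (D²/4)/Var. For power, class means were set at −d/2, 0 and +d/2, with d chosen to give 80% power with arm in the model (noncentral F, 2 and 95 df). Arm was then dropped (2 and 96 df, inflated variance).

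| ρ | d (steps) | Inflation, D = 1200 | Power without arm | Inflation, D = 600 | Power without arm |
|---|---|---|---|---|---|
| 0.3 | 1837 | 1.06 | 77% | 1.02 | 79% |
| 0.5 | 1553 | 1.09 | 76% | 1.02 | 79% |
| 0.7 | 1203 | 1.15 | 74% | 1.04 | 78% |
| 0.8 | 982 | 1.23 | 71% | 1.06 | 78% |
| 0.9 | 694 | 1.45 | 63% | 1.11 | 75% |

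For D = 1200, the standard error of a class mean change rises by √1.09, √1.15 or √1.225, that is 4%, 7% or 11%, at ρ = 0.5, 0.7 or 0.8.

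**5. Direction of the error.** In a simulation with no class difference (20,000 runs, 34 per class, 17 per arm in each class, D = 1200), the rejection rate without arm was 0.042, 0.031 and 0.024 at ρ = 0.5, 0.7 and 0.8. With arm in the model it was 0.054, 0.048 and 0.049. Leaving arm out gives too few rejections, not too many.

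**The case against.** The strongest reply is that the protocol never says one-way. An analysis of variance approach could include arm, and a statistical analysis plan that is not shown may specify it. That stands in part: the class-only model is the natural reading of two parallel one-factor comparisons, but still a reading. It does not cover the two-sample t test, which is a named method and cannot include the stratification factor.

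It can also be said that a valid, conservative test is not an error, that comparing classes is not among the four aims, and that most of the sizing is assumed. All of this is fair, and it is why the point is minor. The 1200 steps is a detectable difference from a power statement. If feedback has no effect, the built-in arm difference does not arise and nothing is lost.

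A reader might infer more than the documents support:

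- *That the class comparison is biased or yields false positives.* Stratification by class year keeps the arms about balanced within class, and the simulation shows a conservative test.
- *That the plan ignores the arm difference in change.* The same sentence tests it separately.
- *That the power claim is undermined.* The 84% concerns the phase 1 arm comparison and is untouched.
- *That the argument covers every endpoint in the sentence.* Weight and survey changes run from July-November 2010 to May 2011, not from phase 1 to phase 2.
- *That adding arm stops a class mean from mixing two exposures.* With balanced arms, the adjusted class contrast is still an average over both.

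**Conclusion.** The point holds as a minor matter of efficiency for step change. On the natural reading, the class-year analysis carries any arm difference in change as error and is less precise than it need be, without being biased. At the planned 1200-step effect, the error variance rises by about 9% to 22%, and 80% power falls to between 76% and 71%, for correlations of 0.5 to 0.8. At 600 steps, power stays at about 78% to 79% over the same range. A large loss (to 63%) needs both the full 1200 steps and a correlation of 0.9. These sizes rest on additive effects, balanced arms and a correlation that the protocol does not state.

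**What to change.** For step change, replace the two separate tests with one linear model: change = arm + class year. Report the class comparison adjusted for arm and the arm comparison adjusted for class year. Also tabulate mean change by arm within each class, so that the gain from feedback plus competition can be read apart from the gain from competition alone; the additive model does not do this by itself.

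The cost is one sentence and the degrees of freedom for the added factor: one when arm joins the class comparison, two when class year joins the arm comparison. No new data or participants are needed.

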### SPECIFIC AIMS

Concisely state the objectives of the study and the hypothesis being tested.

The main objective of this study is to test an intervention to increase the physical activity of medical residents, an employee population with little time for exercise. Specifically, the aims of this study are:

1. To determine if providing medical residents with an activity device that measures steps, distance, and calories burned and tracks this information over time on a website increases residents’ physical activity levels as measured by number of steps per day compared to a control group using a blinded activity device (no feedback).
2. To determine if an unblinded team competition using the activity device directly following the randomized phase increases residents’ activity level compared to baseline.
3. To determine if activity level is associated with change in weight during the residency year.
4. To determine if the average hours of sleep per week is associated with changes in weight and with activity level.

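### The sleep associations of Aim 4 rest on unadjusted correlations, so differences between class years can produce or mask them

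*Protocol*

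**What the plan says.** Aim 4 in the protocol's Specific Aims is "To determine if the average hours of sleep per week is associated with changes in weight and with activity level". Under Research Design and Methods, Statistical methods, the analysis for it is a single sentence: "Pearson or Spearman correlation coefficients will be used to summarize the correlation between sleep time and change in weight/number of steps". It mentions no grouping, covariate, partial correlation or regression.

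Elsewhere the same protocol gives class year (intern, junior, senior) a role in three places:

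- Randomization is stratified by class year (Research study, Randomization).
- Changes in the primary and secondary endpoints, which include steps, weight and sleep, are "compared among the residency year groups using an analysis of variance approach" (Statistical methods).
- For the second phase, "The residents will be divided into 3 teams based on their class: interns, juniors, or seniors", and these teams compete on steps (Team competition phase).

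On the Fitbit sleep and step data, the protocol states: "This data will be collected from all study subjects during both the randomized phase and the team competition phase of the study".

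**The concern.** The protocol treats class year as something that may move steps, weight and sleep, then omits it from the analysis that relates those variables to each other. Suppose one class sleeps less and walks more than another for reasons of rota. A correlation across all residents would then pick up that contrast even if, among residents of the same class, sleep and steps were unrelated. If class differences run against a real within-class association, the crude coefficient shrinks towards zero or changes sign.

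At stake is the interpretation of Aim 4. The Expected Benefits section hopes to learn whether changes in activity go with better sleep habits and prevention of weight gain, and to inform other institutions. A coefficient that may only restate the difference between interns and seniors is weak support for that, and class year is known for every participant.

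**Working it through.** **Inputs from the protocol.** About 100 residents are expected to enroll. The power analysis uses 50 per arm, a difference of 1200 steps, an SD of 2000 and two-sided alpha of 0.05. There are three classes.

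**The plan's own figure.** The only design figure is 84% power for the two-group t-test on steps. The noncentrality is 1200 / (2000 × √(2/50)) = 3.0. With 98 degrees of freedom, power is 84.4% by the noncentral t (85.1% by normal approximation), so the stated figure reproduces. No figure is given for the correlations.

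**Class year: assumptions.** The documents give no class differences in sleep, steps or weight. Take three equal classes with means at −g, 0 and +g within-class SDs. The between-class variance is (2/3)g². With within-class correlation r_w and shifts g₁ (sleep) and g₂ (the other variable), the crude correlation is

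r = [r_w + (2/3)g₁g₂] / √[(1 + (2/3)g₁²)(1 + (2/3)g₂²)].

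This is in SD units, so it applies equally to sleep with steps and to sleep with weight change. Rejection rates come from simulation (N = 100, classes of 33/34/33, 20,000 runs). The crude Pearson test has 98 degrees of freedom and the class-adjusted test 96.

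*No association within class, shifts in the same direction:*

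| g in both variables | crude r | crude test rejects | adjusted test rejects |
|---|---|---|---|
| 0.25 | 0.0417/1.0417 = 0.04 | 6% | about 5% |
| 0.5 | 0.1667/1.1667 = 0.14 | 29% | about 5% |
| 0.75 | 0.375/1.375 = 0.27 | 81% | about 5% |

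Hand check of the middle row by Fisher z: atanh(0.143) × √97 = 1.42, and P(Z > 1.96 − 1.42) is about 29%.

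*Within-class r of 0.30, shifts in opposite directions:*

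| g in both variables | crude r | crude power | adjusted power |
|---|---|---|---|
| 0.25 | (0.30 − 0.0417)/1.0417 = 0.25 | 71% | about 85% |
| 0.5 | (0.30 − 0.1667)/1.1667 = 0.11 | 20% | about 85% |
| 0.75 | (0.30 − 0.375)/1.375 = −0.05 | 7% | about 86% |

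If class shifts only one of the two variables, little is lost. With r_w = 0.30 and shifts of 0.5 and 0, crude r is 0.28 and power is 81% against 86% adjusted.

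**Randomized arm.** With 1:1 allocation, a feedback effect of size d adds d²/4 to the variance of phase 1 steps. At d = 1200 the total SD is √(2000² + 600²) = 2088, so a correlation is multiplied by 2000/2088 = 0.958, and 0.30 becomes 0.287. At d = 600 the factor is 0.989. This is attenuation, not bias, if feedback leaves sleep alone. If feedback also moved sleep by 0.1 to 0.5 SD (assumption), the induced correlation would be only about 0.01 to 0.07.

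**The case against.** **A marginal association is what Aim 4 literally asks for.** If interns sleep less and walk more, then sleep and steps are associated among residents, and a coefficient meant to summarize the correlation reports that correctly. This stands as far as it goes. The rejections tabulated above are errors only if the result is read as holding within a class. The crude coefficient can therefore remain as a description; what is missing is the adjusted one beside it. A reader might go further and infer that the aim concerns changes within a resident over time. The wording does not support that: the comparison is between residents.

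**Adjustment could sit in an analysis plan that is not at hand, and pooling is inferred.** This is partly right. However, the protocol does not leave the method open. It names a simple coefficient, and the sentences before it name arms and residency years where grouping is intended.

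**The size is assumed.** This stands. With shifts of 0.25 SD the crude test rejects 6% of the time instead of 5%. Stratifying on class year does not prove that class predicts sleep or weight, since balance within the later teams is reason enough to stratify.

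**The steps variable is ambiguous.** The sentence can be read as change in steps. Differencing would remove stable class differences in step level, but not class differences in response to the competition.

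**Two stronger readings are tempting.** One is that pooling the arms seriously distorts the result; at the protocol's planned effect it shrinks a steps correlation by about 4%. The other is that Aim 3, "To determine if activity level is associated with change in weight during the residency year", is also answered with a confounded number. The quoted sentence does not pair steps with weight change, so no such number is specified, and a method for that aim may be in the analysis plan. Aim 3 is not part of this point.

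**Conclusion.** The point holds in a limited form. The protocol fixes an unadjusted correlation for Aim 4 while treating class year as a possible driver of the same variables, so class year can create or hide an association. The documents do not show that it will. Under assumed same-direction shifts of 0.25 to 0.75 SD with about 100 residents, rejection without any within-class association runs from about 6% to 81%. Under opposing shifts of the same size, power for a within-class correlation of 0.30 falls from about 85% to between 71% and 7%. The arm contribution is small. The aim is secondary; the randomized comparison of steps and its 84% power are untouched. The change is worth making because it is nearly free, not because the trial's main result depends on it.

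**What to change.** Rewrite the Aim 4 sentence in Statistical methods. Report partial correlations (partial rank correlations where Spearman would be used), or linear regressions of weight change and of steps on average sleep, adjusted for class year. Include randomized arm as a minor precision term. When weight change is the outcome, also adjust for the time between assessments: baseline falls anywhere from July to November 2010 and the final measurement in May 2011, roughly 6 to 10 months apart. State whether steps enters as a level or as a change, and over which phase. Keep the crude coefficient as a description if wanted.

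The cost is one or two sentences and no new data. Of 98 degrees of freedom, class year uses 2, arm 1 and the interval 1, so 3 to 4 in all.
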